## **8.5 SITE ACCREDITATION AND QUALITY CONTROL**

FDG-PET site accreditation and quality assessment will be performed using established procedures by the PET core lab at St. Thomas' Hospital. (Appendix 4)

DCE-PET site accreditation and quality assessment will be performed using established procedures in Mount Vernon Hospital. (Appendix 4)

## 8.6 SYSTEMATIC REVIEW, META-ANALYSIS AND ECONOMICS ASSESSMENT

The primary outcome measures from the prospective observational study (described in section 3.1) are the diagnostic accuracy (sensitivity and specificity) for  $^{18}\text{F}$ FDG-PET/CT and DCE-CT in relation to subsequent clinical diagnosis of lung cancer. Since test results drive clinical management, patients with positive and negative imaging results are anticipated to face different care pathways and different outcomes (depending on whether their condition was correctly or incorrectly characterised). The systematic review and economic evaluation are intended to extend the analysis beyond an assessment of diagnostic accuracy to encompass the clinical utility and cost effectiveness of alternative strategies for diagnosing malignancy in people with solitary pulmonary nodules of greater than 8mm. This will be done in parallel to the current study and the outcomes will inform the development of the economic evaluation and be presented in the final report, through publication in peer review journals and at conferences. The systematic review process will be supported by an expert advisory group that includes relevant clinicians (e.g. chest physician, radiologist) and academics (e.g. methodologists).

Details of the systematic review protocol will be registered with PROSPERO database and can be found in Appendix 5.

## 8.7 ECONOMIC ANALYSIS

To evaluate the cost-effectiveness of the use of DCE-CT in the characterisation of SPNs, we will construct an economic model in accordance with current recommended best practice [23,26]. We propose a two stage format where a decision tree model will be developed to analyse the outcomes of diagnosis. The decision tree model will identify outcomes as: i) malignant SPN correctly diagnosed, ii) malignant SPN misdiagnosed as benign, iii) benign SPN correctly diagnosed, and iv) benign SPN misdiagnosed as malignant. The results of this will inform a Markov model to assess the longer term implications of diagnostic strategies. The Markov model will include health states for malignant disease at diagnosis (based on stage, i.e. local, regional or distant), recurrence (in patients treated with curative intent) and disease-free states (for patients with benign SPN and those with malignant disease who undergo successful surgery) as well as an absorbing “death” state. The perspective will be the NHS and Personal Social Services (PSS). In the long-term model costs and benefits will be discounted using standard rates (3.5%) [23].

Uncertainty relating to input parameters and assumptions will be explored using sensitivity analyses (deterministic, and where appropriate feasible probabilistic). The key variables to be explored will include: estimates of sensitivity and specificity of diagnostic strategies; prior probability (i.e. prevalence) of malignancy (including estimates for patients with SPN detected by CT screening as well as by clinical presentation), costs of diagnostic strategies, cost of curative treatment, probabilities of disease progression in patients with malignant disease and health related quality of life (associated with disease states and with curative treatment).

Four diagnostic strategies will be addressed:  $^{18}\text{F}$ FDG-PET/CT alone, DCE-CT alone, selection for  $^{18}\text{F}$ FDG-PET/CT by preceding DCE-CT and simultaneous DCE-CT/ $^{18}\text{F}$ FDG-PET. We will estimate a variety of outcome measures for use in the economic analysis; these will be cost per correctly characterised SPN and cost per life year gained. In addition, the identification of health-related quality of life data from the literature review will allow the outcome measure for the economic evaluation to be quality adjusted life years (QALYs) as recommended by NICE and the US Panel on Cost-effectiveness in Health and Medicine [23,27]. Where appropriate we will estimate the incremental cost-effectiveness ratio (ICER) of strategies including DCE-CT relative to the reference standard ( $^{18}\text{F}$ FDG-PET/CT alone) – standard decision rules, relating to dominance or extended dominance, will be applied in calculating ICERs. Cost-effectiveness acceptability curves (CEACs) will be generated in any probabilistic sensitivity analysis, to illustrate the probability of the intervention being cost effective over a range of willingness to pay values.

Resource use data will be collected as part of the case review at 24-months. Resource use identified will be costed using appropriate local and national cost data. Another important source of data for the model will be from the results of the systematic review. There will be close collaboration between the systematic review and economic aspects of this study to ensure that data appropriate to the economic model is collected. In addition there will be close collaboration between the economic and clinical members of the team to ensure the model conforms to appropriate clinical realities. Although de novo modelling is planned, the model will be informed with reference to other relevant published economic modelling studies [12-18] and the possibility of adapting an existing published model will be considered. The model will be developed using standard software such as Microsoft Excel and Tree-Age Pro.

## 9 STATISTICS AND DATA ANALYSIS

### 9.1 STATISTICAL PLAN INCLUDING INTERIM ANALYSIS

Of the primary outcome measures in this study, the diagnostic characteristics for DCE-CT and F-DG-PET are used for sample size calculations. Use of the other outcome measures related to economic analyses is prevented by the prior need for detailed characterisation of the decision trees. We consider the sample size needed to detect particular accuracy for each test separately, and then when the tests are used in conjunction.

#### Sample size consideration for each test separately

Published sensitivity for F-DG-PET for the characterisation of SPN vary between 77 and 96% (pooled weighted average: 92%) and specificity varies between 76 and 100% (pooled weighted average: 90%). Published sensitivity and specificity values for DCE-CT vary between 81 and 100% (pooled weighted average: 87%) and 29 and 100% (pooled weighted average: 83%) respectively. Based on two previous UK studies, the mean prevalence of malignancy in indeterminate SPN has been reported as 68.5% [18]. At this prevalence, a sample size of 375 will produce approximately 257 malignant and 118 benign SPNs. This will give confidence limits for sensitivity and specificity of DCE-CT of 87% +/- 4.1% and 83% +/- 6.8% respectively, with sensitivity and specificity values for F-DG-PET of 92% +/- 3.3% and 90% +/- 5.4% respectively. These estimates will provide sufficiently narrow confidence limits to allow precise economic modelling based on the results. For the purposes of economic analyses, we will also consider combining our data with the meta-analysis results from our systematic review (section 8.2), where previous studies we currently know about total 217 patients who had undergone both techniques [8-10]. Recruitment rates are anticipated to be high (70%) because DCE-CT will be additional rather than an alternative to normal care, and is readily incorporated into the existing PET-CT examination. We expect to recruit the required sample size (375) in 18 months. With a 70% recruitment percentage of all meeting the inclusion criteria, in order to recruit 375 patients we need to invite  $375/0.7 = 536$  patients.

#### Sample size consideration for when both tests are used together

Consider if both tests are used together. In particular, (i) those DCE-CT -ve are classed as benign, and (ii) those DCE-CT +ve are then given the F-DG-PET test, with those F-DG-PET +ve classed as 'malignant' and those F-DG-PET -ve classed as 'benign'. The specificity of this process is the same as using F-DG-PET alone. So, the key interest is estimating the sensitivity of this joint test classification strategy compared to F-DG-PET alone. Based on previous data of 130 truly malignant tumour patients, there are 114 that give a DCE-CT +ve and F-DG-PET +ve result; this suggests the sensitivity of the joint testing procedure is  $114 / 130 = 0.877$ . Compared to the F-DG-PET sensitivity thought to be 0.92 (as noted above), the joint testing approach is projected to reduce sensitivity by about 4%. Based on the sample size formula of Alonzo et al. [28], to detect that the joint DCE-CT followed by F-DG-PET approach has at least a 4% reduction in sensitivity compared to the F-DG-PET sensitivity of 0.92, a total sample size of 288 patients is required (including 197 with a truly malignant tumour); this calculation assumes an 80% power, 5% significance

level, and prevalence of malignancy of 0.685. Thus, by including 375 patients are per our previous sample size calculations above, our study is also powered to detect at least a 4% decrease in sensitivity for the joint testing approach.

### Statistical analysis

#### (i) Diagnostic accuracy for 2 year follow-up

We will consider the diagnostic accuracy of positive FDG-PET and DCE-CT, both separately and in conjunction, in relation to a diagnosis of lung cancer by 2 years. In these analyses we will only be able to use those patients for whom the presence of lung cancer by 2 years is known; i.e. those without diagnosed lung cancer who drop-out before the end of 2 years will be excluded. This is likely to be small.

Initially, the separate diagnostic performance of FDG-PET/CT and DCE-CT will be examined using diagnostic criteria defined and over the full range of possible threshold values. At each threshold sensitivity and specificity will be estimated (with 95% confidence intervals), and the Receiver Operator Characteristic (ROC) curve will be calculated. The optimal cut-point from the range of values will be reported based on keeping the sensitivity above 90% and maximising specificity within this limitation. An alternative cut-point that provides the best trade off in sensitivity and specificity will also be reported. The sensitivity, specificity, positive predictive value (PPV) and negative predictive value (NPV) at these cut-points will then be presented with 95% confidence intervals. When translating sensitivity and specificity to PPV and NPV, we will need to assume a particular prevalence. This will be based on the prevalence in our study, and also we will report PPV and NPV for a range of other prevalence's reported in the literature (identified from our systematic review).

Secondly, the diagnostic performance of FDG-PET/CT and DCE-CT combined will also be examined using the same techniques as above; we will class patients as 'positive' if they have both FDG-PET and DCE-CT positive, and all others as 'negative'. Again, a range of different thresholds for both FDG and DCE will be considered.

Thirdly, a logistic regression model will be considered including both PET and CT, on their original scale, as covariates. This may increase the power and diagnostic accuracy of identifying those who will subsequently be diagnosed with lung cancer. It will provide a risk score and predicted probability of lung cancer for each individual, based on their specific test values. We will then use a cut-off value to decide when a risk score is high (such that we predict an adverse outcome) and when it is low (such that we predict a good outcome). The calibration of the model will be assessed by grouping patients into deciles ordered by predicted risk and considering the agreement between the mean predicted risk and the observed number of true lung cancer cases in each decile (sometimes referred to as the expected versus observed statistic, E/O). The derived diagnostic rule will be cross validated by comparing the classification of each patient with their actual primary outcome of confirmed lung cancer, allowing an estimate of the sensitivity and specificity of the prediction model. Then, by varying the chosen cut-off level, we will produce a receiver operating characteristic (ROC) curve summarising the sensitivity and specificity of the predictive rule across the range of cut-offs. The overall discriminatory ability will be summarised as the Area Under ROC curve (AUC) with 95% confidence interval. The most suitable cut-off level can then also be detected. The internal validity of the final model will also be assessed by the bootstrap re-sampling technique to adjust for over-optimism in the estimation of model performance due to validation in the same dataset that was used to develop the model itself.

If the above methods all show poor accuracy performance (in terms of calibration and/or discrimination), then the logistic regression model will be extended to include additional patient-level covariates (such as time from FDG injection to PET-CT scan), in addition to test results. Demographic information will be considered here as well as clinical and imaging features considered indicative of a higher likelihood of SPN malignancy than unselected patients. The performance of the model will also be evaluated at the

practice-level where possible, to ascertain whether model performance is consistent in each practice or, if not, the variability in performance across practices, and whether it can be improved by tailoring the prevalence used in each practice.

(ii) Flexible parametric analysis for lung cancer risk including those who drop-out before 2 years

To include any censored observations (i.e. those who were lost to follow-up before the end of 2 years and had not been diagnosed with lung cancer) a survival analysis will also be considered. This will account for the length of follow-up for each individual (regardless of their length of follow-up), and the exact time of their lung cancer diagnosis or censoring point. Kaplan-Meier plots will, if appropriate, be presented with log-rank tests to compare between the positive and negative diagnoses. In addition, we will use a flexible parametric survival analysis [29,30], that flexibly models the baseline hazard using restricted cubic splines, and computes hazard ratios for each test (on their continuous or dichotomised scale, as included), which are very similar to those from a Cox regression (which does not provide the baseline hazard though). Using the baseline hazard and hazard ratios from the fitted model – in a similar manner to the logistic regression approach described above – this will produce a risk score and a probability of being diagnosed with lung cancer by 2 years for individuals with a particular test values (or combination of test values). Calibration and discrimination of the model at 2 years of follow-up can then be checked back at the individual level. For example, for each patient their own predicted probability of being diagnosed with lung cancer by 2 years will be available from the model. Then, for each decile of predicted risk, the expected (E) probability of lung cancer will be compared with the observed (O) probability of lung cancer as obtained from a Kaplan-Meier curve of the patients in that decile. In each decile, the E/O statistic should be close to 1 if the performance of the model is consistently good across deciles. In other words, the calibration slope should be 1. The C statistic will also be calculated to examine discrimination. Bootstrapping and shrinkage methods will be used, if appropriate, to reduce over-optimism from developing and validating the model on the same set of observations. Finally, the performance of the model will be evaluated at the practice-level where possible, to ascertain whether model performance is consistent in each practice or, if not, the variability in performance across practices.

Interim analysis and data storage

No interim analysis is planned for this study

Data and all appropriate documentation will be stored for a minimum of 15 years after the completion of the trial, including the follow-up period.

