### **5.4 ACCESS TO OUTCOME DATA**

If patients are lost to follow up within 2 years (e.g. relocation to another health authority) outcome data will be obtained via the Health and Social Care Information Centre. Consent for this will be taken during initial consenting process.

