## **7 DEFINITION OF END OF TRIAL**

This is a non-CTIMP study with all eligible patients recruited consecutively into the study and undergoing each study procedure. Recruitment will be terminated once 375 patients have been recruited and undergone a DCE-CT scan.

The study has two possible endpoints for each patient:

**Either** the diagnosis of lung cancer via biopsy **or** a diagnosis of benign or non- lung cancer via either biopsy (please note that in this case economic data collection will continue to be required for 2 years follow up)

**Or** failure of the imaged nodule to progress (increase in size) during the 2 year follow up period.

The end of the study will be reached when the last study patient reaches two years of follow up or withdraws full consent for continuing in the study.

**PLEASE NOTE:** *Health Resource Data will be collected for all patients over a 2 year period following the DCE-CT scan, therefore the end of study form will not be completed until this time unless patients have withdrawn full consent.*

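### The exclusion rule for the 2-year accuracy analysis is wider than its own criterion and, read literally, drops patients already known not to have lung cancer

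*Protocol*

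**What the plan says.** Section 9.1, Statistical analysis (i), gives the criterion for the accuracy analysis as known lung cancer status at 2 years. The same sentence then explains it, by an i.e. clause, as "those without diagnosed lung cancer who drop-out before the end of 2 years will be excluded". The protocol expects few such patients and gives no rate. PPV and NPV are to be calculated at the study prevalence and also at prevalences from the literature.

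Other sections bear on who is known not to have lung cancer:

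- Section 8.4 accepts pathology and/or 24-month imaging as the reference standard.
- Section 7 lists "a diagnosis of benign or non- lung cancer via either biopsy" as a patient endpoint, with follow-up to 2 years continuing for economic data.
- Section 5.4 states that for patients lost within 2 years "outcome data will be obtained via the Health and Social Care Information Centre".
- Section 5.5 allows results of procedures done before a full withdrawal of consent to be recorded.

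Section 9.1 (ii) says a survival analysis will be considered, so as to include as censored "those who were lost to follow-up before the end of 2 years and had not been diagnosed with lung cancer".

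**The concern.** The criterion and its explanation define different analysis sets. A patient with benign histology who withdraws at month 6 has a reference result under section 8.4 and an endpoint under section 7. That patient meets the criterion but falls inside the exclusion. A patient with a lung cancer biopsy who withdraws at the same time is kept. A patient lost to the site whose 2-year outcome is recovered under section 5.4 is in a similar position: the status is known, but no sentence returns a recovered non-case to the analysis.

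Two analysts could therefore build different sets for a primary outcome. The one who follows the clause removes known patients from the non-cancer column only, which is the smaller one. That column fixes specificity and, through the study prevalence, the study-based PPV and NPV.

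**Working it through.** **Inputs.** All come from section 9.1, sample size for each test separately: "At this prevalence, a sample size of 375 will produce approximately 257 malignant and 118 benign SPNs"; "confidence limits for sensitivity and specificity of DCE-CT of 87% +/- 4.1% and 83% +/- 6.8% respectively"; and, for FDG-PET, values "of 92% +/- 3.3% and 90% +/- 5.4% respectively". The 118 benign nodules stand in for the non-cases. The number of early leavers is my assumption, since none is stated.

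**Step 1: the plan's own figures.** 375 × 0.685 = 256.9, so 257 malignant and 118 benign. Half-widths from 1.96 × √(p(1−p)/n) are 4.11 and 6.78 points for DCE-CT, and 3.32 and 5.41 points for PET. All agree with the protocol.

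**Step 2: drop k known non-cases, with loss unrelated to the test result, and keep all 257 cancers.** Let B = 118 − k.

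- Prevalence = 257/(257 + B)
- PPV = se × 257/(se × 257 + (1 − sp) × B)
- NPV = sp × B/(sp × B + (1 − se) × 257)
- Accuracy = (se × 257 + sp × B)/(257 + B)

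For DCE-CT (87%/83%) with k = 12: true negatives 0.83 × 106 = 87.98, false negatives 0.13 × 257 = 33.41, NPV = 87.98/121.39 = 72.5%.

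| k | B | Prevalence | DCE-CT PPV | DCE-CT NPV | DCE-CT accuracy | PET NPV |
|---|---|---|---|---|---|---|
| 0 | 118 | 68.5% | 91.8% | 74.6% | 85.7% | 83.8% |
| 6 (5%) | 112 | 69.6% | 92.2% | 73.6% | 85.8% | 83.1% |
| 12 (10%) | 106 | 70.8% | 92.5% | 72.5% | 85.8% | 82.3% |

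Even at a 30% loss of benign patients, DCE-CT accuracy is 86.0%, a change of 0.3 points.

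**Step 3: how much is due to the wording.** Suppose 12 non-cases leave and 6 of them have a known result. The literal rule gives prevalence 70.8% and DCE-CT NPV 72.5%. Keeping the 6 gives 69.6% and 73.6%. The wording then accounts for just over 1 point in each. The rest comes from patients with no result, who are excluded either way.

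**Step 4: specificity.** Loss unrelated to the test result leaves it at 83% and only widens the interval (half-width 6.8 to 7.1 points at 10% loss). With the planned 97.94 true negatives and 20.06 false positives for DCE-CT:

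- 10% of test-negative non-cases dropped: 88.15/(88.15 + 20.06) = 81.5% (PET 89.0%)
- 10% of test-positive non-cases dropped: 97.94/(97.94 + 18.05) = 84.4% (PET 90.9%)

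The direction depends on which non-cases leave.

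**The case against.** The strongest reply is that known status governs the sentence, so a sensible analyst would keep a benign biopsy, and a patient with a recovered outcome need not count as a drop-out at all. A reader might infer from the clause that the protocol has decided to discard known benign results. It has not: no sentence says so, and the stated criterion points the other way. What remains is that the clause is the only operational definition given, it contradicts the criterion it explains, and section 9.1 (ii) describes its censored group in the same terms without an exception.

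Three further inferences should be resisted.

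- The rule does not keep every cancer patient who leaves, only those already diagnosed. Cancers undiagnosed at exit are excluded too, which could affect sensitivity: losing 5 that were test-negative would raise apparent DCE-CT sensitivity from 87% to 223.59/252 = 88.7%.
- Section 9.1 (ii) does not say that lost patients are censored at the date of loss. It refers to a censoring point without defining it.
- Nothing states that recovered data may add cancers but never non-cancers.

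There is also mitigation. PPV and NPV are reported at literature prevalences as well, and sections 5.4 and 5.5 should keep the number with missing outcomes low. This limits the effect but does not correct the study-prevalence figures. The survival analysis helps little, because it is only to be considered and, on its wording, would treat a known benign patient as censored.

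**Conclusion.** The point holds as an internal contradiction in a stated analysis rule, with a modest effect that cannot be fixed from the protocol. If the clause is followed, study prevalence and study-based PPV are too high and study-based NPV too low. Under the assumed losses of 5% to 10% of non-cases, the shift is about 1 to 2 points in prevalence and in DCE-CT NPV. That is the most the wording could cause at those losses, reached only if every leaver had a known result.

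A reader might go further and conclude that specificity and accuracy are biased as well. The protocol does not support that in general. Specificity is biased only if loss among non-cases depends on the test result. Section 8.6 makes this plausible by expecting different care pathways for positive and negative patients, but the direction is open. The change in accuracy is negligible.

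**What to change.** In section 9.1 (i), replace the i.e. clause with a rule such as: patients are excluded only if no reference-standard result was reached; patients with definitive benign or other non-lung-cancer pathology are included as non-cases whenever they left.

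In addition:

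- Include patients whose recovered outcome data cover month 24, with a sensitivity analysis that omits those without 24-month imaging.
- In section 9.1 (ii), state one follow-up coverage rule and apply it alike to cases and non-cases.
- Report the remaining exclusions by the result of each test, so that a reader can judge whether specificity or sensitivity may be affected.

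The cost is a few sentences of analysis wording and no new data collection. The one downside is that recovered non-cases without a 24-month CT fall short of the imaging standard in section 8.4, which is why the sensitivity analysis is needed.

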### Secondary Objectives:

- To assess within an NHS setting, the incremental value of incorporating the CT appearances of a SPN into the interpretation of integrated PET/CT examinations.
- To assess whether combining DCE-CT with FDG-PET/CT is more accurate and/or cost-effective, in the characterisation of SPNs, than either test used alone or in series.
- To document the nature and incidence of incidental extra-thoracic findings on FDG-PET/CT and DCE-CT undertaken for the characterisation of SPNs and model their impact on cost-effectiveness.

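### The protocol claims power for the joint rule's sensitivity against PET alone, but no analysis it states estimates that paired difference

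*Protocol*

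**What the plan says.** The first part of the sample-size text in Section 9.1 sets 375 patients (about 257 malignant and 118 benign at a prevalence of 68.5%) so that each test's sensitivity and specificity has a narrow interval.

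The second part takes up the joint rule: DCE-CT negatives are called benign, and DCE-CT positives are classified by PET. It says: "So, the key interest is estimating the sensitivity of this joint test classification strategy compared to" PET alone. From earlier data, "the joint testing approach is projected to reduce sensitivity by about 4" points. Using a cited formula for comparing two medical tests, it states the requirement as "sensitivity of 0.92, a total sample size of 288 patients is required (including 197 with a truly malignant tumour"), and concludes that "our study is also powered to detect at least a 4% decrease in sensitivity for the joint testing approach". The same paragraph says the joint rule has the specificity of PET alone.

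The analysis text, part (i), starts with "Initially, the separate diagnostic performance of" the two tests, giving sensitivity, specificity and predictive values with 95% confidence intervals. Then the performance of PET/CT and "DCE-CT combined will also be examined using the same techniques as above"; for this, "we will class patients as 'positive' if they have both" tests positive. The rest of (i) and part (ii) add logistic and survival models. The only comparative test named is a log-rank test between positive and negative diagnoses.

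Section 2 has a comparative secondary objective: whether combining the tests "is more accurate and/or cost-effective, in the characterisation of SPNs, than either test used alone or in series".

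**The concern.** One part of Section 9.1 names a comparison, calls it the key interest and claims power for it. The next part prescribes analyses that do not contain it. A sensitivity with its own interval for PET, and another for the joint rule, do not together give the precision of the difference, because both classifications are made in the same patients and are strongly correlated.

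If only the stated analyses are reported, the contrast between the joint rule and PET is left to be read from two intervals that will nearly always overlap. The claimed power then attaches to no stated result, and the comparative objective is answered less precisely than the data allow.

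**Working it through.** **Inputs, all from Section 9.1.** PET sensitivity 0.92; loss 4 points, so joint sensitivity 0.88 (the earlier data give 114/130 = 0.877); power 80%; significance 5%; prevalence 0.685; 257 malignant and 118 benign planned; DCE-CT sensitivity 0.87 and specificity 0.83; PET specificity 0.90. Sidedness is not stated; two-sided is assumed.

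**1. Reproducing 197 and 288.** The protocol does not print its formula. The paired relative-sensitivity form is

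n = [(z₀.₉₇₅ + z₀.₈₀)/ln g]² × [(g + 1)·S_PET − 2·P_both] / (g·S_PET²), with g = 0.88/0.92.

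A joint positive must be PET positive, so P_both = 0.88. Then (2.8016/−0.04445)² = 3972.2; the numerator is 1.80 − 1.76 = 0.04; the denominator is 0.8096. The result is 196.25, so 197 malignant, and 197/0.685 = 287.6, so 288. Both match.

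Other readings do not match:

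| Assumption | Malignant needed |
|---|---|
| One-sided | 155 |
| Joint sensitivity 0.877 | 183 |
| 4% relative loss | 214 |
| Tests conditionally independent (P_both = 0.88 × 0.92) | 888 |
| Two independent groups | 882 per group |

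The claimed power therefore rests on full use of the pairing.

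**2. What the stated analysis gives at 257 malignant.** Half-width = 1.96·√[p(1 − p)/257].

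- PET 0.92: ±3.3 points, 88.7 to 95.3%.
- Joint 0.88: ±4.0 points, 84.0 to 92.0% (at 0.877: 83.7 to 91.7%).

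The intervals overlap. In 200,000 simulated trials with 257 malignant patients and cell probabilities 0.88 (both positive), 0.04 (PET only) and 0.08 (neither), the two intervals failed to overlap in about 0.7% of trials.

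**3. What the paired contrast gives.** At a common PET threshold all discordance runs one way, so the loss is a simple proportion: malignant nodules that are PET positive and DCE-CT negative, over all malignant nodules.

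- A loss of 0.92 − 0.877 = 0.043 is about 11 of 257 = 4.3%, with an exact (Clopper-Pearson) 95% interval of 2.2 to 7.5%.
- At a true loss of 0.04 the standard error is √[(0.04 − 0.04²)/257] = 1.22 points, giving about 1.6 to 6.4 points. Ignoring the pairing, it is √[(0.92·0.08 + 0.88·0.12)/257] = 2.64 points, giving about −1.2 to 9.2.
- An exact McNemar test needs at least 6 one-way discordant cases (2 × 0.5⁶ = 0.031). Its power is 94.6% at 257 and 80.3% at 197; the simulation gave 94.5%. A comparison of two independent groups of 257 would have 32.7%.

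**4. DCE-CT against PET.** Let j be the proportion of cancers positive on both tests, b = 0.92 − j and c = 0.87 − j. The paired half-width is 1.96·√[(b + c − (b − c)²)/257].

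| j | Half-width, points |
|---|---|
| 0.87 (the maximum possible) | 2.7 |
| 0.86 | 3.2 |
| 0.84 | 4.0 |
| 0.80 (conditional independence) | 5.3 |
| Pairing ignored | 5.3 |

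The earlier data's 0.877 cannot be used for j here, because j cannot exceed a DCE-CT sensitivity of 0.87.

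**5. Specificity of the joint rule.** A benign nodule is a joint false positive only if both tests are positive. At a common PET threshold, joint specificity = PET specificity + P(PET positive and DCE-CT negative, given benign). With PET specificity 0.90, the added term lies between 0 and 10 points, depending on how many of the roughly 12 PET-positive benign nodules (0.10 × 118) are DCE-CT negative. Equality is one extreme, not the general case.

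**The case against.** The strongest reply is that the interval or test for a paired difference is ordinary SAP content, and that the SAP is not at hand. Section 9.1 already says the comparison is intended and cites a formula for comparative studies, and separate intervals are the right analysis for the first primary objective, which is precise performance of each test. That last point stands. The reply does not clear the rest: Section 9.1 does not defer its analysis. It goes into cut-point rules, calibration by decile and bootstrapping, and it prescribes the single-test method for the combined rule. A protocol that claims power for a contrast should name that contrast among its analyses.

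Several stronger readings are tempting and are not supported:

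- A reader might infer that 375 was set for the paired comparison. It was set for single-test precision; the paired calculation needs 288 and is a second claim on the same patients.
- A reader might infer that the protocol will judge the difference by interval overlap, or compare the tests as independent samples. It says neither.
- A reader might infer that joint sensitivity can never exceed that of PET. This holds only at one shared PET threshold. The analysis explores many thresholds and has a rule keeping sensitivity above 90%; if cut-points are chosen separately, the nesting fails and the one-way 11/257 interval no longer applies.
- A reader might infer that pairing halves the interval for DCE-CT against PET. The gain runs from about half to nil, depending on concordance.
- A reader might want the upper limit of the loss made the main comparison. The protocol gives no acceptable margin, so that would be a preference.

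Two limits of scope also stand. The powered rule is the in-series strategy, which the secondary objective uses as a comparator, so reporting this contrast does not answer that objective in full. And the economic model already sets the strategies against PET/CT, so the trade-off between sensitivity and specificity is partly handled there.

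**Conclusion.** The mismatch holds. The protocol's power statement is arithmetically correct, but only for a paired, nested comparison of the joint rule with PET alone, and that comparison is not among the analyses it states. At 257 malignant nodules the separate intervals would almost always overlap under the assumed 4-point loss, whereas a paired analysis would detect it in about 95% of trials and bound it to within a few points. Because a nested rule cannot gain sensitivity, the estimated loss with its interval is more useful than a test of no difference.

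This rests on the protocol's own values (0.92 and 0.88, prevalence 0.685), a two-sided 5% level and a common PET threshold. The primary single-test analyses are unaffected. The claim that the joint rule's specificity equals that of PET alone is also wrong as a general statement.

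**What to change.** Add to the analysis text of Section 9.1, for example:

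*At a PET threshold and a DCE-CT threshold stated in advance, with the same PET threshold on both sides of the contrast, the paired difference in sensitivity among malignant nodules and in specificity among benign nodules will be reported for the joint rule against PET/CT and for DCE-CT against PET/CT, each with a 95% confidence interval based on the discordant counts.*

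In the joint-testing sample-size paragraph, replace the statement on specificity: at a common PET threshold the joint rule's specificity is at least that of PET alone, and higher whenever a PET-positive benign nodule is DCE-CT negative. Do not quote a fixed precision gain for DCE-CT against PET/CT; give the range of about 2.7 to 5.3 points at 257 malignant nodules.

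The cost is a few sentences and the choice of thresholds in advance. Both scans are already planned for every patient (Section 5.1), so no data, visits or patients are added.
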